## Abstract

**Introduction:**

Alcohol consumption that damages health remains highly prevalent in Sweden despite macrolevel intervention measures such as availability, restrictions and taxation. As understanding of behaviour change develops, there may be an opportunity to enhance individual level interventions by targeting personal dimensions of behaviour, such as underlying motives for drinking alcohol and readiness to change behaviour. This protocol describes a randomised controlled trial aimed at estimating the effectiveness of an intervention tailored to motives and readiness to change.

**Methods and analysis:**

A three-arm, parallel groups, randomised controlled trial will be used to estimate the effects of a motives and readiness to change tailored intervention. We will use a Bayesian sequential design to decide when to stop recruitment, with target criteria for benefit, harm and futility. Recruitment will be completed via web adverts and social media. Inclusion criteria are being aged 18 or older, having access to a mobile phone and being classified as a risky drinker. Participants allocated to the two intervention groups will receive either a personalised digital intervention or an intervention with enhanced tailoring for motives and readiness to change. The personalised intervention consists of weekly screening, personalised feedback and tools for planning behaviour. The enhanced tailored version will follow the same logic but will contain materials tailored for individuals’ drinking motives and readiness to change. The control group will be redirected to two national websites with information about alcohol and health. Outcome measures are weekly alcohol consumption and monthly heavy drinking episodes, which will be contrasted with regression models and estimated using Bayesian inference.

**Ethics and dissemination:**

Ethical approval was obtained from the Swedish Ethical Review Authority on 16 April 2024, (Dnr 2024-01630-01). The results of the study will be disseminated in academic journals and research conferences.

**Trial registration number:**

The trial was preregistered in the ISRCTN Registry on 12 June 2024 (ISRCTN87600318).

STRENGTHS AND LIMITATIONS OF THIS STUDYDouble-blind randomised design enables valid estimation of effects for an intervention tailored to match personal dimensions of behaviour for alcohol outcomes.The use of a Bayesian sequential design will ensure that the trial will not be underpowered or recruit more participants than necessary.Self-report measures will be used which may bias estimates due to social desirability and recall.Mediators will be assessed using single, face-valid items in lieu of validated questionnaires to reduce participant burden.

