## Methods and analysis

To address the study objectives, we will conduct a three-arm (1:1:1), parallel groups, RCT. The study received ethical approval from the Swedish Ethical Review Authority (16 April 2024, Dnr 2024-01630-01) and was prospectively registered in the ISRCTN trial registry on 12 June 2024 (ISRCTN87600318). This protocol has been written following Standard Protocol Items: Recommendations for Interventional Trials (SPIRIT) guidelines.^49^ Recruitment started in February 2025 and is planned to not extend beyond February 2026.

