### Sample size

This trial will use a Bayesian sequential design to avoid under-recruitment and over-recruitment.^65^,^68^ Bayesian sequential designs use target criteria which are evaluated continuously as data are made available, and recruitment ends once the criteria are considered sufficiently fulfilled. Throughout the study period, we will model the primary outcomes according to the analysis plan, and regression coefficients representing the effect of allocation to enhanced tailored versus personalised intervention at the 4-month interval will be asserted against target criteria for benefit, harm and futility. Note that relative differences between groups are estimated as incidence rate ratios for primary outcomes. We will aim to have one criterion fulfilled per primary outcome measure. In the case of futility, two additional criteria will be considered where intervention groups are combined and contrasted against the control group. The criteria for ending recruitment are:

Weekly alcohol consumption benefit/harm: the posterior probability is greater than 95% that past week’s alcohol consumption is *less/greater* in the enhanced tailored intervention group versus the personalised intervention group.

Frequency of heavy episodic drinking benefit/harm: the posterior probability is greater than 95% that the number of episodes of heavy drinking is *fewer/more* in the enhanced tailored intervention group versus the personalised intervention group.

Weekly alcohol consumption futility: the posterior probability is greater than 95% that the relative difference in past week’s alcohol consumption between the enhanced tailored intervention group versus the personalised intervention group is less than 15%.

Frequency of heavy episodic drinking futility: the posterior probability is greater than 95% that the relative difference in the number of episodes of heavy drinking between the enhanced tailored intervention group and the personalised intervention group is less than 15%.

In case of futility—benefit/harm versus controls: the posterior probability is greater than 95% that past week’s alcohol consumption is *less/greater* and number of episodes of heavy drinking are *fewer/more* in the intervention groups combined versus controls.

In case of futility—futility versus controls: the posterior probability is greater than 95% that the relative difference in both primary outcome measures between the combined intervention groups and the controls is less than 15%.

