While the final sample size is not determined a-priori in Bayesian group sequential designs, we conducted a series of simulations with effect sizes of 15% weekly alcohol consumption difference. The code for the simulations can be found in online supplemental Appendix D. Simulations suggested that approximately 1750–2200 participants will be necessary to recruit. Since this is an online trial of digital interventions, we require minimal resources per recruited participant; thus, resources are available even if the sample size required is larger than anticipated.

There are a few considerations on the above design: first, the criteria added if the primary contrast is found futile will be used to decide when to stop recruiting in case the available evidence suggests that the contrast against controls is worth considering further. The rationale for this is due to this trial employing a longer follow-up interval (8 months) than our previous trial of the personalised intervention (which stopped at 4 months), and the current trial attempting to blind participants; thus, evidence gaps can be addressed by continuing recruitment in this case. Second, by using Student’s t priors centred at the null, estimates will be pulled towards the null when data is scarce, protecting against spurious and potentially erroneous findings.^68^ Third, due to the nature of Bayesian inference, there is no need to adjust analyses for multiple looks at the data.^69^ Fourth, since no sample size is prespecified, we reduce the risk of stopping recruitment both too early and too late,^65 68 70^ while also allowing the trial to be stopped if the intervention is deemed harmful. Finally, from previous and ongoing trials using online recruitment with this type of design,^16 71 72^ we anticipate that recruitment will not last for more than 12 months.

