### Limitations

This trial will have minimal barriers to participation and, therefore, we anticipate that follow-up attrition will be a major limitation. To reduce attrition as much as possible, we will use a follow-up routine involving reminder texts and phone calls, which we have successfully used before.^16 71 82^ The Bayesian sequential design we use in this trial will ensure that we keep recruiting participants until we have satisfied the recruitment criteria, thus preserving precision in our statistical estimates. However, this does not protect against attrition bias stemming from systematic missingness. We have planned to study attrition in our ancillary analyses and use multiple imputations to see how findings are sensitive to missing data.

We will attempt to keep participants blind throughout the trial. The study is advertised as one that evaluates digital support, but neither the advertisement nor the informed consent materials provide details about the nature of the support. This blinding is likely to be successful for the two intervention groups. However, controls will be given material they have likely come across online before, which may make them realise that they are, in fact, controls. We will nevertheless attempt to blind controls in this study to attend to a limitation of the previously conducted trial of the personalised version of the digital intervention.^16 20^ That trial used a waiting list group as a control, which may induce bias due to research participation effects.^8083^,^85^ The decision to use this procedure also presents an ethical risk, as those who sign up seeking help to reduce their drinking will be asked to use online resources that do not comprise proven effective intervention materials. To partially mitigate the risk, we will make the personalised intervention available to controls once they have completed their trial participation.

We use outcome measures related to alcohol consumption as primary in this trial as the interventions are designed to reduce alcohol consumption. However, for some individuals, for instance those with coping motives, it may be more relevant to focus more on reduced alcohol-related problems and less on consumption. We acknowledge that this trial will be limited in its ability to discover these nuances.

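### The sequential design cannot guarantee that the trial is neither underpowered nor over-recruited: stopping is judged on a 4-month effect while recruitment continues, and the planned end date is not reconciled with recruiting until the criteria are met

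*Protocol article*

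**What the plan says.** The strengths and limitations box, after the abstract, presents the property as certain: "The use of a Bayesian sequential design will ensure that the trial will not be underpowered or recruit more participants than necessary". The Limitations section is equally firm that the design "will ensure that we keep recruiting participants until we have satisfied the recruitment criteria".

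The Sample size section sets the stopping rule. Criteria are "evaluated continuously as data are made available, and recruitment ends once the criteria are considered sufficiently fulfilled". The quantity monitored is "the effect of allocation to enhanced tailored versus personalised intervention at the 4-month interval", and the section adds "We will aim to have one criterion fulfilled per primary outcome measure". No pause in recruitment is described. The expected size is given as "Simulations suggested that approximately 1750–2200 participants will be necessary to recruit", from simulations at a 15% difference in weekly consumption.

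On timing, Methods and analysis says "Recruitment started in February 2025 and is planned to not extend beyond February 2026". The Sample size section expects recruitment to last 12 months at most, but also says that resources exist for a larger sample. It describes the benefit of the design more cautiously, as a lower risk of stopping too early or too late. Ethics and dissemination expects the complete data set by October 2026.

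**The concern.** Two of the article's own statements sit badly with the guarantee.

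First, the deciding outcome arrives 4 months after randomisation. At any stop after month 4, the people randomised in the last 4 months have not supplied it. By the design's own rule, they were enrolled beyond the number whose data settled the question.

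Second, a calendar end to recruitment and recruitment until the criteria are met cannot both be assured. If the date prevails, the trial may close with a primary outcome unresolved, which is what the box says cannot happen. If the criteria prevail, the February and October 2026 dates are not reliable.

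What is at stake is a stated strength that readers and funders may take at face value, and a missing statement of what is reported if no criterion is met.

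**Working it through.** **Inputs from the article.** Expected recruitment 1750–2200; allocation 1:1:1; recruitment window February 2025 to February 2026, about 12 months; stopping outcome at 4 months; posterior probability threshold 95%; futility margin 15%; simulated effect 15%, so log rate ratio ln 0.85 = −0.1625.

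**Not given, so assumed.** Uniform accrual, log-scale variance per participant, correlation between the two outcomes, and attrition.

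**1. The plan's own figure.** The range 1750–2200 cannot be formally reproduced, because the article gives no dispersion, mean count, power or attrition rate, and the simulation appendix is not shown. It can be checked for plausibility. Take one-sided 0.05 as the analogue of a posterior above 95%. The variance implied by a total N is

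v = (N/3) × [0.1625 / (z₀.₉₅ + z_power)]² / 2.

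- At 80% power (1.645 + 0.842), N = 1750 gives v = 1.25 and N = 2200 gives v = 1.57.
- At 90% power, the values are 0.90 and 1.13.

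**2. Overrun at stopping.** Overrun = monthly accrual × 4.

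- 1750/12 = 146 per month; × 4 = 583.
- 2200/12 = 183 per month; × 4 = 733.
- This is one third of a 12-month total, so 1167–1467 people have reached 4 months when recruitment is planned to end.
- If the same totals accrue in 9 months, the overrun is 778–978, or 44%.

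These counts need no assumption about variance or attrition, only about accrual.

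**3. Information at the planned end of recruitment.** Let the variance give 80% power per outcome at the stated N. With 8/12 of the data, the standardised effect is 2.486 × √(8/12) = 2.030, and power is Φ(2.030 − 1.645) = 65%. This describes the last look, not the final analysis.

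**4. Chance that no criterion is met on both outcomes if February 2026 binds.** This is a normal-approximation simulation of enhanced versus personalised: 20,000 runs, monthly looks, v = 1.25 (N = 1750) and 1.57 (N = 2200), outcome correlation 0.6, flat prior. Each outcome must meet benefit, harm or futility (rate ratio between 0.85 and 1/0.85) at the same look. Recruitment stops at month 12, and all recruited participants are then followed to 4 months.

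| True rate ratio (both outcomes) | Attrition | Not met by month 12 | Still not met after all mature |
|---|---|---|---|
| 0.85 | 0% | 35–36% | 17–18% |
| 0.85 | 30% | 49–50% | 33–34% |
| 0.92 | 0% | 67–68% | 40–41% |
| 0.92 | 30% | 77% | 65% |
| 1.00 | 0% | 81% | 41% |
| 1.00 | 30% | 88% | 75% |

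The last column is the relevant one, because late recruits still contribute 4-month data. The simulation leaves out any borrowing from 2-month data and the extra criteria against control that apply after futility.

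**5. The dates side by side.** February 2026 plus the 8-month follow-up is October 2026, so the data set date depends on recruitment ending as planned. The Limitations section and the remark about resources point to open-ended recruitment. The article does not say which governs.

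**The case against.** The strongest reply is that the article states no hard cap. The end date is a plan, the 12 months an expectation, resources for a larger sample are said to exist, and the criteria are something the trial aims to fulfil. This stands. A reader might infer that the trial is bound to stop in February 2026 and will be underpowered, but the text does not support that. The percentages in step 4 apply only if the date binds. The lag does not itself cause underpowering either, since people in follow-up at the stop still add to the final 4-month analysis.

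A reader might also infer that these later data could overturn the trial's conclusion. The documents do not support this. The criteria are listed as rules for ending recruitment, and the analyses are to be done once the data set is complete, so no verdict is declared at the stopping look.

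Nor can it be said that the sample size simulation ignores the lag. The appendix is not shown, and on its face the 1750–2200 is a number to recruit.

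The late recruits are not wasted: they add precision at 4 and 8 months, and 2-month responses inform the multilevel model indirectly. None of this removes the lag or makes the guarantee true. The softer claim in the Sample size section is defensible, but it differs from the claim in the box.

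**Conclusion.** The concern holds as an overstated property and an unreconciled timetable. It does not show that the design is invalid.

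- **Over-recruitment.** The guarantee fails outright. Any stop after month 4 carries about 4 months of accrual beyond the people who informed it: 583–733 if 1750–2200 are accrued evenly over 12 months. Confidence is high.
- **Underpowering.** The guarantee fails only if February 2026 is binding, which the article leaves open. In that case about 17–34% of trials at a true rate ratio of 0.85 would end with the rule unmet after all participants mature. That range is illustrative: it rests on a variance chosen to give 80% power per outcome at the stated N, a correlation of 0.6 and 0–30% attrition.

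**What to change.** 1. In the strengths box and in Limitations, replace the guarantee with the claim in the Sample size section, that the design reduces the risk of stopping too early or too late.
2. In Sample size, state that about 4 months of accrual is expected to be enrolled beyond the deciding data at any stop, and give the number.
3. Reconcile Methods and analysis, Limitations, and Ethics and dissemination by saying whether February 2026 is binding. If it is, state that a trial with no criterion met is reported as inconclusive, and give the simulated probability of that outcome. If it is not, make the October 2026 date conditional.
4. Confirm that the simulation behind 1750–2200 accounts for the 4-month lag, and restate the figure if it does not.

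The cost is a few sentences and a simulation check. No participants are added, and the design, estimand and analysis model do not change. The downside is a less favourable stated property.

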## Introduction

 Approximately 81% of adults in Sweden report consuming alcohol in the past 12 months,^1^ with more than 40% drinking at levels that, according to guidelines, indicate risky alcohol use.^2^ Although there is no safe drinking limit,^3 4^ drinking at risky levels significantly increases the likelihood of experiencing adverse health and social consequences, including cancer, liver cirrhosis, violence, accidents and injuries.^5^ The annual societal costs associated with alcohol consumption in Sweden have been estimated to total €9.4 billion.^6^ Thus, reducing alcohol consumption in the general population could lead to a reduction of the societal burden caused by drinking.

Considering this, Sweden has adopted several macrolevel measures to reduce the prevalence of risky drinking, including taxation, sales restrictions and governance of alcohol ad campaigns.^7^ Despite these measures, the prevalence of risky drinking has remained consistent over the last 15 years,^1^ suggesting these efforts may have reached their limit. A recent development in preventing alcohol-related harm using macrolevel means is the update to drinking guidelines by the National Board of Health and Welfare,^8^ whereby the threshold for indicating risky drinking, which was previously defined separately for men and women, is now the same for all individuals. According to the updated guidelines, risky drinking is indicated when an individual consumes 10 standard drinks or more per week (120 g) or consumes four or more standard drinks in a single drinking session (48 g) at least once a month.

Nonetheless, using stricter guidelines to limit risky drinking and consequent harms is not guaranteed to be a viable prevention measure. Evidence from an international study suggests that individuals adopt a subjective approach to gauging alcohol limits, often reaching almost double the typically recommended guidelines, on average 88 g for men and 70 g for women per drinking session.^9^ Given this discrepancy between recommended consumption limits and behaviour, prevention efforts may benefit from focusing on the individual rather than relying on this particular macrolevel means of change alone, that is, providing public health measures that support change rather than only informing about guidelines.

In addition to guidelines for risky drinking, the National Board of Health and Welfare recommends that health and medical services should offer counselling or other support to those who engage in risky drinking. However, there are low levels of provision of guidance on health-compromising behaviours, such as alcohol consumption—only 1–5% of patients in primary care settings have historically been offered advice.^10^ One reason is the continued shortage of licensed health practitioners,^11^ leading to insufficient human resources to address patients’ immediate health concerns and health promotion in day-to-day practice. In addition, the lack of utilisation of treatment for risky alcohol use and alcohol use disorders is well documented.^12^ This may be reflective of the stigma associated with seeking support for alcohol problems.^13^ Considering this, offering individual-level interventions that support behaviour change while overcoming potential implementation barriers could play an important part in reducing alcohol-related harm.^14^,^16^

One such means of individual-level support is brief alcohol interventions. Brief alcohol interventions assess alcohol use and provide feedback, advice and support for behaviour change.^17 18^ Studies have found that providing brief alcohol interventions digitally (eg, through email, texts and apps) can be an effective method to reduce both weekly consumption and heavy episodic drinking.^19^ Furthermore, the digital mode of delivery of these interventions may increase reach and reduce the stigma associated with seeking help as they are, often, anonymous.

A recent randomised controlled trial (RCT) estimated the effectiveness of a personalised digital alcohol intervention among Swedish adults who sought help online.^16 20 21^ The intervention targeted improvements in motivation and self-efficacy, while teaching new skills to change behaviour. After 4 months, those assigned to the intervention consumed 23% less alcohol than those assigned to basic health information, along with reporting 29% fewer episodes of heavy drinking. This suggests that digital interventions could play a role in a strengthened response to the consistently high prevalence of alcohol consumption in the Swedish population. Nonetheless, individuals vary in what they need from interventions;^22^ for example, the effectiveness of treatments is often predicated on individual characteristics such as motivation, personality, genetics, gender, age and social factors.^23^,^28^ Hence, effectiveness may be improved by increasing the tailoring of interventions to the individual.

Extant literature regarding the matching of treatments for alcohol use disorders to individual patient characteristics has produced mixed results.^23 24 27^ The discrepancies across the literature may be due to various factors, including the heterogeneity of alcohol use disorders (eg, variance in severity, comorbidities, social support, drinking patterns),^29^ the interaction of patient characteristics,^30^ therapist effects^31^ and overlapping of treatment effects.^32^ Despite the mixed findings, there is practical potential for adopting a personalised approach to behaviour change. For example, even small moderation effects can result in a meaningful change at the individual level, such as increased abstinence, less relapsing and increased adherence.^24^ Results from Project MATCH (Matching Alcoholism Treatments to Client Heterogeneity) support this; individuals with low motivation assigned to motivational enhancement therapy (MET) had better outcomes than those assigned to cognitive behavioural therapy,^24^ while individuals with high trait anger had better outcomes when engaging with less directive therapies (eg, MET or the 12 steps).^23^ Furthermore, psychological factors have been shown to moderate treatment effects. For example, individuals with a high readiness to change had better outcomes than individuals scoring low in the construct.^33^ This again highlights the potential for personalisation of alcohol interventions, especially as psychological constructs are typically modifiable.^34^ In consideration of this, we propose to estimate the effectiveness of a brief digital alcohol intervention that has been tailored to provide content along dimensions of personal behaviour, in this case individuals’ underlying motives for consuming alcohol and their readiness to change current behavioural patterns.

Drinking motives have been demonstrated to be a proximal driver of alcohol consumption, which acts as a gateway for other more distal drivers, such as alcohol expectancies.^35^,^37^ Motives are linked to engagement with various drinking patterns. For example, social and enhancement motives are linked to heavy episodic and risky drinking, and coping motives have been linked with problem drinking.^38^,^40^ Motives are also linked to subsequent alcohol-related consequences. For example, coping motives are linked with impaired control, physiological dependence and poor self-care, while enhancement motives are linked with antisocial behaviour and blackouts.^41^ Social motives for drinking are linked with accidents and injuries and poor academic performance,^42^ and conformity motives with mental health and sleep problems.^43^ Furthermore, motives have been shown to interact with situational contexts to impact consumption. For example, individuals who drink for social or enhancement reasons report consuming more alcohol in social contexts, while those who drink for coping reasons report increased frequency in non-social contexts (eg, drinking at home alone).^35 44^ Finally, motives have been shown to interact with context to influence planned and unplanned drinking.^45^ This suggests that motives may be an apt target for alcohol intervention, but also that each motive may need a different approach to supporting changes in alcohol behaviours. By tailoring to individuals’ motives, we may be able to appropriately match content to needs, which may in turn result in alcohol behaviour change. For example, those reporting coping motives may drink to relieve stress or anxiety,^46^ so it may be appropriate to teach skills that enable them to relieve negative affect without drinking alcohol.

Furthermore, an intervention can be tailored to match an individual’s readiness to change their drinking behaviour. Process of change models, such as the Transtheoretical Model^47^ or the Health Action Process Approach,^48^ point towards a continuum of change an individual will iteratively progress through before a longer-term change in behaviour is established and maintained. These models present a valuable framework for designing and implementing health behaviour change interventions that can be tailored to meet individual needs and in turn result in greater effectiveness. For example, a brief intervention may be ineffective if the individual is not ready to change. However, if the content is tailored to target and address ambivalence for change, it may meet the individual’s specific needs for facilitating change.^47^

In this study, we will investigate a digital alcohol intervention tailored to individuals’ motives for drinking and readiness to change. The primary aim of the study is to estimate the intervention’s effectiveness in terms of weekly alcohol consumption and frequency of heavy episodic drinking among Swedish adults who are looking for help online. The enhanced tailored intervention will be contrasted against two comparators: (1) the existing personalised intervention, which was previously found to be effective,^16^ and (2) referral to online resources that would typically be found when looking online. Secondary aims of the study include estimating the degree to which the effects of the interventions are mediated through mechanisms of behaviour change and estimating individual-level effects.

